## Abstract

**Background:**

Acute cerebral infarction (ACI), being the predominant form of stroke, presents challenges in terms of the limited effectiveness of various treatments in improving the neurological function. Although acupuncture shows promise in addressing ACI, the availability of high-quality evidence regarding its efficacy, safety, and underlying mechanism remains insufficient. In this study, we design a multicenter, prospective, single-blind, randomized controlled trial with the aim of evaluating the efficacy and safety of acupuncture for ACI, making an attempt to unveil the molecular mechanisms by proteomic.

**Methods:**

A total of 132 patients involving four hospitals will be randomized at a 1:1:1 ratio in the acupuncture group, control group, and sham acupuncture group. All the patients will receive basic treatment, and the patients in the acupuncture and sham acupuncture groups will also receive either acupuncture or sham acupuncture treatment, respectively, at six sessions each week for a 2 weeks period, followed by 3 months of follow-up. The primary outcome will be the change in the National Institute of Health Stroke Scale (NIHSS) scores after treatment. The secondary outcomes will include the Fugl-Meyer Assessment (FMA) scale scores and the Barthel Index (BI). Adverse events that occur during the trial will be documented. To discover differentially expressed proteins (DEPs) and their roles between the ACI subjects and healthy controls, we will also perform 4D-DIA quantitative proteomics analysis, and the DEPs will be confirmed by enzyme-linked immunosorbent assay (ELISA). This study was approved by the institutional review board of the First Teaching Hospital of Tianjin University of Traditional Chinese Medicine (TYLL2023043). Written informed consent from patients is required. This trial is registered in the Chinese Clinical Trial Registry (ChiCTR2300079204). Trial results will be published in a peer-reviewed academic journal.

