### Estimation of sample size

2.4

In this study, we aim to compare the difference in the NIHSS score between the acupuncture group and sham acupuncture group after the treatment. Sample size calculations were performed for a simple comparison of the two groups. According to a previous study (Sun and Wu, 2019), the NIHSS scores of mean ± SD between the two groups were 6.2 ± 2.1 and 4.9 ± 1.8, respectively, after the treatment. A total of 36 participants per treatment group (108 in total) were required when setting a one-sided test with *α* = 0.025, *β* = 0.20. To compensate for a 20% loss to follow-up, the sample size was increased to 44 participants in each group.

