#### Primary outcomes

2.7.1

The primary outcome we chose in this study is the NIHSS score that will be measured before and after treatment to evaluate the neurological deficit. There are 15 items in the scale including consciousness, best gaze, motor arm, facia palsy, motor leg, limb ataxia, sensation ability, dysphagia, and neglect. The score of each item scores range from 0 to 4, and the total scores range from 0 to 42. A higher score indicate a more severe neurological deficit.

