### Statistical analyses

2.8

Quantitative variables will be presented with mean ± SD. The Shapiro–Wilk test and box plots will be used to assess the homogeneity of the quantitative variables. All continuous and independent variables in the groups will be performed by Student’s *t*-test at baseline. The Mann–Whitney U test will be selected if the variance was not homogeneous between two groups. Stata software will be used to analyze the data according to the intention-to-treat principle, and a two-sided *p*-value less than 0.05 was considered significant.

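### The primary outcome is change in NIHSS in the abstract but the post-treatment score in the sample size, and the only t-test stated is tied to baseline; one endpoint and one baseline-adjusted primary analysis should be named

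*Protocol article*

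**What the plan says.** Four places in the protocol article bear on the primary comparison.

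- **Abstract, Methods:** "The primary outcome will be the change in the National Institute of Health Stroke Scale (NIHSS) scores after treatment".
- **Section 2.4, Estimation of sample size:** "we aim to compare the difference in the NIHSS score between the acupuncture group and sham acupuncture group after the treatment". The inputs are post-treatment values: "the NIHSS scores of mean ± SD between the two groups were 6.2 ± 2.1 and 4.9 ± 1.8, respectively, after the treatment". The error rates are given as "setting a one-sided test with *α* = 0.025, *β* = 0.20", and the result is "A total of 36 participants per treatment group (108 in total) were required", raised to 44 per group for loss to follow-up.
- **Section 2.7.1, Primary outcomes:** "The primary outcome we chose in this study is the NIHSS score that will be measured before and after treatment". It does not say whether the score after treatment or the difference from baseline is analysed.
- **Section 2.8, Statistical analyses:** "All continuous and independent variables in the groups will be performed by" Student's t-test, and the sentence ends by placing that test at baseline. Mann-Whitney is named as the alternative when variances differ between two groups. The section names no test for the post-treatment primary comparison and no baseline covariate.

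**The concern.** Change from baseline and post-treatment score are different variables with different SDs. A power statement derived from the SD of one does not carry over to the other without the baseline SD and the baseline-to-post correlation.

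The two unadjusted estimates also differ. The between-arm difference in change equals the between-arm difference in post-treatment score minus the chance difference at baseline. If the text supports both, the primary result can depend on which is picked once the data are known.

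The testing sentence does not settle the matter. A t-test at baseline in a randomised trial examines the allocation, not the treatment effect. Baseline NIHSS is collected in every patient and is plausibly prognostic, so a method that uses it is available at almost no cost.

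**Working it through.** **Inputs from the document.** Post-treatment means 6.2 and 4.9, so the difference is 1.3; SDs 2.1 and 1.8; one-sided alpha 0.025, which has the same critical value as the two-sided 0.05 in Section 2.8; power 80%; 36 per group before loss; entry NIHSS from 5 to below 15 (Section 2.2.2).

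**Inputs not in the document, so assumed.** Baseline SD (sb) and baseline-to-post correlation (r).

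**Step 1: reproduce the plan's figure.** Pooled SD = sqrt((2.1² + 1.8²)/2) = 1.956. By the normal approximation, n = 2 × (1.956 × (1.960 + 0.842)/1.3)² = 35.5, so 36 per group, as stated. With the t distribution it is 37, and power at 36 is 79%. The plan's figure is right for an unadjusted comparison of post-treatment scores.

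**Step 2: change score at 36 per group.** SD(change) = sqrt(sb² + 1.956² − 2 × r × sb × 1.956). The true difference stays at 1.3, because randomisation makes the expected baseline difference zero. Two baseline SDs are tried: one equal to the post-treatment SD (1.956), and 2.87, the SD of a uniform spread over the integer scores 5 to 14 (sqrt((10² − 1)/12) = 2.87).

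**Step 3: ANCOVA at 36 per group.** Residual SD = 1.956 × sqrt(1 − r²), which does not depend on the baseline SD.

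Power by the noncentral t, two-sided 0.05:

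| r | Change, sb = 1.956 | Change, sb = 2.87 | ANCOVA |
|---|---|---|---|
| 0.3 | 65% (SD 2.31) | 45% (SD 2.95) | 83% (SD 1.87) |
| 0.5 | 79% (SD 1.96) | 57% (SD 2.54) | 89% (SD 1.69) |
| 0.7 | 95% (SD 1.52) | 76% (SD 2.05) | 97% (SD 1.40) |
| 0.8 | 99% (SD 1.24) | 87% (SD 1.76) | over 99% (SD 1.17) |

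Change has the same SD as the post-treatment score when r = sb/(2 × 1.956). That is r = 0.50 with equal SDs and r = 0.73 with sb = 2.87. Below that value a change analysis has less power than planned; above it, more.

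**Step 4: how far the two unadjusted estimates can differ.** They differ by the chance baseline difference, whose standard error is sb × sqrt(2/36): 0.46 for sb = 1.956 and 0.68 for sb = 2.87. The 95% range is therefore about ±0.9 to ±1.3 NIHSS points, against a target effect of 1.3.

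**Step 5: why ANCOVA removes the ambiguity.** With baseline NIHSS in the model, subtracting baseline from the outcome only shifts the baseline coefficient by one. The arm coefficient and its standard error are identical for score and change.

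**The case against.** The strongest reply is that only the abstract says change. Section 2.4 states the comparison plainly as the score after treatment, and the stated number is correct for it. On that view the defect is one abstract sentence at odds with the body. Much of this stands: the body does not fix change as the endpoint, so this is an unresolved inconsistency and not a settled change endpoint with wrong power. But Section 2.7.1, which should decide it, names measurement both before and after treatment and leaves it open.

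Three stronger readings are tempting, and the document does not support them.

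- *The trial is underpowered.* This cannot be shown. The direction depends on a correlation and a baseline SD that are not given. The low figures need a wide baseline spread, and the eligibility criterion gives a range, not a distribution. Even with sb = 2.87, power is 87% at r = 0.8.
- *Baseline NIHSS will be ignored.* That would be read from silence. A condensed article may leave covariates to the analysis plan, and Section 2.8 does not rule out adjustment.
- *The baseline t-test is the only test.* Mann-Whitney is also named, in a sentence that does not itself mention baseline.

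It is also fair to say that an unadjusted comparison of post-treatment scores is valid under randomisation: it is unbiased, and its confidence interval allows for chance imbalance. ANCOVA is recommended here because it is more efficient and resolves the conflict, not because the unadjusted test is an error. It is not entirely free either: with r near zero, the covariate costs a degree of freedom for no gain.

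**Conclusion.** The point holds as an inconsistency in the primary endpoint together with a misdirected testing sentence. The abstract names change, the sample size is built on the post-treatment score, Section 2.7.1 does not choose, and Section 2.8 ties its t-test to the one time point at which no treatment effect can exist.

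The 80% power is correct for the unadjusted post-treatment comparison and is not demonstrated for change. The power range for change, from 45% to 95% across r = 0.3 to 0.7 and the two baseline SDs, shows how much the choice could matter. It is not an estimate of what this trial will have. Under the same assumptions ANCOVA keeps or raises power at 36 per group (83% to 97%). This should be fixed; nothing here shows the sample size to be inadequate.

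**What to change.** 1. State one primary endpoint in the same words in the abstract and in Sections 2.4 and 2.7.1.
2. In Section 2.8, name the primary analysis: an ANCOVA of the 2-week NIHSS on arm with baseline NIHSS as covariate, for acupuncture versus sham, reporting the adjusted difference with its 95% CI.
3. Replace the baseline t-test sentence with a descriptive baseline table by arm.
4. Add to Section 2.4 that 36 per group was derived for the unadjusted post-treatment score.

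Adjusting for centre, and using the same model for the FMA and BI with their own baselines, are reasonable options but are not needed to settle this point.

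The cost is a few sentences and one degree of freedom, with no new data and no new patients. The change should be made before treatment allocation is unblinded.

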**Discussion:**

The results of this study will determine the preliminary efficacy and safety of acupuncture in ACI patients and whether the mechanism of this form of non-pharmacologic stimulation is mediated by a novel therapeutic target for neurorehabilitation through our proteomic analysis.

**Clinical trial registration:**

https://www.chictr.org.cn, identifier ChiCTR2300079204.

## Introduction

1

Acute cerebral infarction (ACI) is the predominant form of stroke, comprising 60–80% of all stroke cases. It is also recognized as the second leading cause of death and the major cause of disability worldwide (Naghavi et al., 2017). The Global Burden of Disease Study has revealed an upward trend in the incidence of ischemic stroke in China, with rates escalating from 117 per 100,000 individuals in 2005 to 145 per 100,000 individuals in 2019 (GBD 2019 Stroke Collaborators, 2021). In addition, the American Heart Association’s report on Heart Disease and Stroke Statistics in 2020 indicates that the prevalence of stroke in the United States was 2.5% in 2016 (Virani et al., 2020). Patients with ACI experience alterations in their lifestyle, which subsequently impacts their overall quality of life (Pan et al., 2008; Wu et al., 2014). These alterations encompass various aspects such as physical wellbeing, psychological state, social interactions, and personal beliefs (Sainsbury and Heatley, 2005). It is widely recognized that neuroprotection holds promise as a therapeutic strategy for individuals affected by ACI. The occurrence and progression of ACI involve multiple pathological and physiological mechanisms, including excitotoxicity, oxidative and nitrosative stress, cellular apoptosis, and inflammation (Lipton, 1999; Chamorro et al., 2016). Acupuncture, a significant component of traditional Chinese medicine, has emerged as a potentially efficacious non-pharmacological intervention for the management of ACI. Acupuncture has exhibited diverse neuroprotective and reparative properties that contribute to its anti-inflammatory (Cao et al., 2021) and anti-apoptotic effects (Tian and Wang, 2019) and its ability to promote angiogenesis (Zhang et al., 2020). The findings from a robust randomized controlled trial involving 862 participants in the early stage of stroke have demonstrated that the addition of acupuncture to standard care leads to a reduction in mortality compared with standard care alone (Zhang et al., 2015a). Numerous reviews have demonstrated the prospective effectiveness and safety of acupuncture in addressing ACI and its subsequent complications. According to a comprehensive examination of literature and perspectives (Qin et al., 2022), it has been observed that acupuncture facilitates the regeneration of nerve cells, thereby promoting the replacement of non-functional cells after a stroke. This process ultimately leads to the restructuring of neural connections and the restoration of functional abilities. Furthermore, a systematic review (Sang et al., 2022) has indicated that acupuncture therapy administered during the sub-acute phase of ischemic stroke may improve language function in individuals with aphasia. Moreover, another systematic review (Wang et al., 2012) has demonstrated that scalp acupuncture exhibits superior efficacy in terms of improving neurological deficit scores and clinical effectiveness compared with western conventional medicine in patients with ACI. Nevertheless, it remains challenging to derive definitive conclusions based on the currently accessible evidence. Further large-scale, well-designed randomized clinical trials on this topic are still warranted (Wong et al., 2012; Zhang et al., 2013a; Li et al., 2014a).

Since “time is brain,” the prompt identification of cerebral ischemia is crucial in the acute phase of onset. Biomarkers serve as objective indicators for evaluating normal or pathological processes, assessing responses to medical interventions, and predicting outcomes (Atkinson et al., 2001). There are already few studies that analyze variations of blood biomarkers after treatment with acupuncture in patients affected by ACI. A recent study (Cui and Jia, 2022) demonstrated that acupuncture in patients with ACI cause an increase in the serum levels of malondialdehyde, superoxide dismutase, and glutathione peroxidase, and another clinical trial (Zhang et al., 2013b) reported a decrease in the levels of serum neuron-specific enolase, soluble protein-100β, and endothelin in ACI patients treated with electroacupuncture. Based on these findings, we hypothesized that alterations in the proteomic profile of blood following acupuncture interventions may potentially mirror neural modifications in individuals diagnosed with ACI.

In light of the ambiguous mechanism and uncertain effectiveness of acupuncture in treating ACI, this randomized clinical trial was devised to assess the safety and efficacy of acupuncture. Additionally, the proteomic analysis will be employed to investigate the potential underlying mechanism. Considering the potential variations in protein expression levels that may arise from acupuncture intervention, the initial set of differentially expressed proteins (DEPs) will be classified based on their associations with specific pathways and then confirmed by the enzyme-linked immunosorbent assay (ELISA) techniques. The validation procedure will be predicated upon the “threshold” of variation of the expression levels, taking into account the findings of previous studies of our team (Du et al., 2011; Li et al., 2014b, 2017, 2022, 2023) and the available relevant literature.

## Methods

2

### Study design

2.1

This is a multicenter, prospective, single-blind, randomized controlled trial that will be conducted in four centers in China. The trial design was approved by the Institutional Review Board of the First Teaching Hospital of Tianjin University of Traditional Chinese Medicine (Tianjin, China) and registered at www.chictr.org.cn (ChiCTR2300079204) in December 2023. This study will be conducted in accordance with the latest version of the Declaration of Helsinki, the Consolidated Standards of Reporting Trials (Schulz et al., 2010), and the Standards for Reporting Interventions in Controlled Trials of Acupuncture guidelines (Macpherson et al., 2010) in trial designing and reporting.

### Participant recruitment

2.2

The eligible consecutive participants will be enrolled in the First Teaching Hospital of Tianjin University of Traditional Chinese Medicine, Tianjin Huanhu Hospital, First Hospital of Jilin University, and Huzhou Central Hospital. This trial will include an enrollment and allocation period of 6 days every week over a 2 weeks intervention period followed by a 3 months follow-up period. The gender- and age-matched healthy people will also be enrolled as the health group that will be analyzed by proteomic analysis investigations. We will obtain the informed consent from each participant or an appointed legal representative if the participant lacks the decision-making capacity. The flowchart of the study is shown in Figure 1, and the mechanism exploration procedure is shown in Figure 2.

**Figure 1 fig1:**
[figure not shown]
A flowchart of the study.

**Figure 2 fig2:**
[figure not shown]
Study design and workflow. AG, acupuncture group; HG, health group; DDA, data-dependent acquisition; DIA, data-independent acquisition.

#### The diagnostic criteria

2.2.1

The diagnostic criteria will be designed in accordance with the Chinese guidelines for the diagnosis and treatment of acute ischemic stroke 2018 (Chinese Society of Neurology, & Chinese Stroke Society, 2018).

#### The inclusion criteria

2.2.2

The inclusion criteria are as follows: (1) individuals who satisfy the established diagnostic criteria for the ailment may be considered for inclusion in the therapeutic intervention; (2) an initial manifestation of the ailment; (3) progression of the ailment within a time frame of 72 h; (4) an age range of 40–75 years with no restrictions based on gender; (5) an NIHSS score ranging from 5 to less than 15; and (6) willingness to participate voluntarily and provision of a duly signed informed consent.

#### The exclusion criteria

2.2.3

The exclusion criteria are as follows: (1) individuals failing to meet the established inclusion criteria; (2) impairment of the Vesta channel’s functionality resulting from craniocerebral trauma, tumors, and other etiologies; (3) assessment of the impact of acupuncture treatment or other therapeutic medications administered within a 3 months period prior to admission; (4) presence of consciousness disorders, deafness, severe depression, schizophrenia, and inability to cooperate; (5) coexistence of severe primary diseases affecting the cardiovascular, neurological, respiratory, hepatic, and renal systems; (6) severe dermatological conditions or hypersensitivity to the investigational treatment; (7) pregnant, lactating, or expecting women; and (8) patients concurrently participating in other research studies.

### Randomization and blinding

2.3

The eligible participants will be enrolled and divided randomly in the acupuncture group (received acupuncture), the control group (received no acupuncture), or the sham acupuncture group (received sham acupuncture) at a ratio of 1:1:1 (*n* = 132) using a computer-generated randomization method. Random numbers were put into an opaque envelope and sealed, and the corresponding serial numbers were affixed to the surface of the envelope for random grouping and concealing. The envelopes were opened according to the order in which the subjects were enrolled for grouping and treatment. The patients will be informed whether they will receive acupuncture treatment or not.

The participants in the acupuncture group and sham acupuncture group will be blinded, while those in the control group will not be. Due to the particularity of acupuncture treatment, it is impossible to blind the acupuncturists in this study. All study personnel including the outcome assessors and data analysts will be blinded to the treatment allocation.

### Estimation of sample size

2.4

In this study, we aim to compare the difference in the NIHSS score between the acupuncture group and sham acupuncture group after the treatment. Sample size calculations were performed for a simple comparison of the two groups. According to a previous study (Sun and Wu, 2019), the NIHSS scores of mean ± SD between the two groups were 6.2 ± 2.1 and 4.9 ± 1.8, respectively, after the treatment. A total of 36 participants per treatment group (108 in total) were required when setting a one-sided test with *α* = 0.025, *β* = 0.20. To compensate for a 20% loss to follow-up, the sample size was increased to 44 participants in each group.

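### Randomising 44 per group with a 20% loss leaves about 35, one short of the 36 the plan requires; the effect on power is under one percentage point

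*Protocol article*

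**What the plan says.** Section 2.4 (Estimation of sample size) of the protocol article sizes the trial on post-treatment NIHSS in the acupuncture and sham acupuncture groups. The planning values come from an earlier study: "the NIHSS scores of mean ± SD between the two groups were 6.2 ± 2.1 and 4.9 ± 1.8, respectively, after the treatment". With beta 0.20 and a one-sided alpha of 0.025, the section concludes: "A total of 36 participants per treatment group (108 in total) were required".

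It then makes the allowance for attrition: "To compensate for a 20% loss to follow-up, the sample size was increased to 44 participants in each group".

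The abstract carries the result forward as the trial size: "A total of 132 patients involving four hospitals will be randomized at a 1:1:1 ratio". Section 2.3 repeats the total of 132. The article gives neither an inflation formula nor a rounding rule.

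**The concern.** Section 2.4 fixes three numbers: the number required (36 per group), the loss rate (20%) and the number randomised (44 per group). Any two of them determine the third, apart from rounding. Compensating for a 20% loss means that the remaining 80% should still reach the required number, and 80% of 44 does not reach 36.

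At stake is whether the sample size statement is correct as reported. It promises a stated power after a stated loss at a stated trial size, and a reader with a calculator will find that the three do not agree.

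**Working it through.** **Inputs, all from section 2.4.** Means 6.2 and 4.9, so the difference is 1.3. SDs 2.1 and 1.8. One-sided alpha 0.025 (z = 1.96). Beta 0.20 (z = 0.8416). Loss 20%. Randomised 44 per group.

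**Step 1: reproduce the plan's 36.** For two independent means under the normal approximation,

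n per group = (z_alpha + z_beta)² × (SD1² + SD2²) / difference²

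= (1.96 + 0.8416)² × (2.1² + 1.8²) / 1.3²

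= 7.849 × 7.65 / 1.69 = 35.53, rounded up to 36.

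The stated 36 is reproduced. A two-sided test at 0.05 gives the same number.

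**Step 2: the attrition allowance.**

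- Needed to retain 36 after 20% loss: 36 / (1 − 0.20) = 45 per group, 3 × 45 = 135 in total.
- Stated: 44 per group, 3 × 44 = 132 in total.
- Expected to remain from 44: 44 × 0.8 = 35.2.
- Loss that 44 can absorb and still leave 36: 1 − 36/44 = 18.2%.

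The shortfall in the number randomised is 1 per group, 3 overall.

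**Step 3: what this does to power.** With the same approximation, power = Φ(difference / √((SD1² + SD2²)/n) − 1.96).

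| n per group | Power |
|---|---|
| 36 | 80.5% |
| 35.2 (expected at 20% loss) | 79.6% |
| 35 | 79.4% |

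**Step 4: how 44 could have arisen.** At least two routes lead to it:

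- 36 × 1.2 = 43.2, rounded up to 44.
- 35.53 / 0.8 = 44.41, rounded to the nearest whole number, 44.

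The first uses the wrong inflation factor. The second uses the right one on the unrounded requirement and then rounds down. In both cases 44 × 0.8 = 35.2, which is below 36 and also below the unrounded 35.53.

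**The case against.** The strongest reply is that the gap is a matter of rounding. Measured against the unrounded requirement, 35.2 falls short of 35.53 by 0.33 of a patient per group. Power of 79.6% rounds to the stated 80%, and the 20% loss rate is itself a round planning guess. All of this stands, and it limits how much weight the point can carry. It does not make the sentence correct, because the article presents 36, not 35.53, as the requirement, and 44 falls short of either after a 20% loss.

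Nor can the mismatch be put down to the article being a condensed account. The requirement, the loss rate and the result are all printed, so the point concerns a stated figure and not an omitted detail.

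A reader might infer three stronger things that the document does not support:

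- **That the sponsor multiplied by 1.2 where it should have divided by 0.8.** This would explain 44, but the article gives no formula, and division by 0.8 followed by rounding to nearest explains it equally well.
- **That 36 is itself too low because a t-test needs more.** Section 2.8 names Student's t-test for baseline comparisons and does not assign it to the post-treatment NIHSS comparison. Section 2.4 refers only to a simple two-group comparison, and its 36 is reproduced by the normal approximation. The 36 is not an error.
- **That baseline adjustment would make 132 sufficient.** That needs a correlation between baseline and post-treatment NIHSS, which the article does not give.

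**Conclusion.** The point holds as a minor arithmetic error. A requirement of 36 per group, a 20% loss and 44 randomised per group cannot all be true. The discrepancy is one patient per group (three in total), or equivalently an 18.2% tolerable loss where 20% is claimed. Power at 20% loss is 79.4% to 79.6%, so the deficit against 80% is at most 0.6 percentage points.

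It would be wrong to read this as a materially underpowered trial: no design choice, analysis or conclusion turns on it. The result rests on the planning means and SDs in section 2.4, the normal approximation that reproduces the plan's own 36, and the plan's own premise that lost patients do not contribute to the comparison.

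**What to change.** Keep 132 patients and correct the last sentence of section 2.4 in one of two ways:

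- state that 44 per group allows for about 18% loss to follow-up while keeping 36; or
- keep the 20% loss and state that power is then about 79%.

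In either case, add the inflation formula and rounding rule that were used. The cost is one sentence, with no additional patients and no change to the design.

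If the sponsor prefers to keep both the 36 and the 20% as written, the matching figure is 45 per group (135 in total). That costs three more patients and a change wherever 132 appears.
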